# Effects of lower extremity constraint-induced movement therapy on gait and balance of chronic hemiparetic patients after stroke: description of a study protocol for a randomized controlled clinical trial

**DOI:** 10.1186/s13063-021-05424-0

**Published:** 2021-07-19

**Keywords:** Stroke, Constraint-induced movement therapy, Gait, Balance, Hemiparesis

## Abstract

**Background:**

Protocols involving intensive practice have shown positive outcomes. Constraint induced movement therapy (CIT) appears to be one of the best options for better outcomes in upper limb rehabilitation, but we still have little data about lower extremity constraint-induced movement therapy (LE-CIT) and its effects on gait and balance.

**Objective:**

To evaluate the effects of an LE-CIT protocol on gait functionality and balance in chronic hemiparetic patients following a stroke.

**Methods:**

The study adopts a randomized, controlled, single-blinded study design. Forty-two patients, who suffered a stroke, who were in the chronic phase of recovery (>6 months), with gait disability (no community gait), and who were able to walk at least 10 m with or without the advice or support of 1 person, will be randomly allocated to 2 groups: the LE-CIT group or the control group (intensive conventional therapy). People will be excluded if they have speech deficits that render them unable to understand and/or answer properly to evaluation scales and exercises selected for the protocol and/or if they have suffered any clinical event between the screening and the beginning of the protocol. Outcome will be assessed at baseline (T0), immediately after the intervention (T1), and after 6 months (T2). The outcome measures chosen for this trial are as follows: 6-min walk test (6minWT), 10-m walk test (10mWT), timed up and go (TUG), 3-D gait analysis (3DGA), Mini Balance Evaluation Systems Test (Mini-BESTest), and as a secondary measure, Lower Extremity Motor Activity Log will be evaluated (LE-MAL). The participants in both groups will receive 15 consecutive days of daily exercise. The participants in the LE-CIT group will be submitted to this protocol 2.5 h/day for 15 consecutive days. It will include (1) intensive supervised training, (2) use of shaping as strategy for motor training, and (3) application of a transfer package (plus 30 min). The control group will receive conventional physiotherapy for 2.5 h/day over 15 consecutive days (the same period as the CIT intervention). Repeated measures analyses will be made to compare differences and define clinically relevant changes between groups.

**Results:**

Data collection is currently on-going and results are expected in 2021.

**Discussion:**

LE-CIT seems to be a good protocol for inclusion into stroke survivors’ rehabilitation as it has all the components needed for positive results, as well as intensity and transference of gains to daily life activities.

**Trial registration:**

www.ensaiosclinicos.gov.brRBR-467cv6. Registered on 10 October 2017. “Effects of Lower Extremities - Constraint Induced Therapy on gait and balance function in chronic hemipretic post-stroke patients”.

**Supplementary Information:**

The online version contains supplementary material available at 10.1186/s13063-021-05424-0.

## Background

Cardiovascular disease is the leading cause of death in the world, representing 31% of the total number of deaths in 2017 [1]. Stroke accounts for almost half of these deaths [1] which means that it is the second greatest cause of death around the world [2] and the third most common cause of disability [3]. Hemiplegia is often the most common sequel caused by stroke, compromising independence in mobility at home or in the community, which sometimes results in losing premorbid society roles and requiring care for a long period of time [4].

Studies have reported that 6 months after the injury, 30% of patients are still unable to walk without assistance [5–7], and 1 year after the event (with relatively good recuperation), half of these patients are still not able to complete the 6-min walk test, walking just 40% of the predicted distance [7]. Despite all rehabilitative efforts, 35% of patients with initial paralysis in lower limbs are still unable to recover a functional gait and 25% are not able to walk without external aid [8]. Thus, within physiotherapy services, the majority of interventions involve approaches to gait training [9].

Protocols involving intensive practice have shown positive outcomes. Constraint induced movement therapy (CIT) appears to be one of the best options for better outcomes in upper limb rehabilitation. Experimental studies in the 1960s using CIT demonstrated that monkeys that suffered sensory deafferentation of their forelimb and then acquired learned non-use were able to use that paw again after having their unimpaired limb constrained for a number of days [10].

A growing number of studies have since supported the efficacy of CIT in upper limb rehabilitation for patients with chronic hemiparesis caused by stroke, which has been recognized and recommended within the treatment sets for this population [11–13]. Moreover, it has been considered the most effective physiotherapy approach for getting better rehabilitation outcomes for paretic upper limbs [14, 15].

CIT has been defined as a “therapeutic package” consisting of different numbers of compounds of combined treatment, used in a systematic and integrated way to engage the patient in using their affected limb for many hours per day over 2–3 consecutive weeks [16]. One of the main advantages of CIT in relation to the various different approaches used in neurological rehabilitation is that it is focused on the behavioral aspects of the method (monitoring, self-efficacy, solving problems, and contractual intervention); this guarantees the active participation of patient during the entire protocol [16].

The current CIT protocol consists of 3 main elements with multiple components and sub-components: (1) repetitive and task-oriented training (diary training with supervision), (2) behavioral strategies (transference package), and (3) constraint of affected limb (for upper extremity protocol) and/or any method to constantly remind the participant to use their more affected limb [16–18].

Post-stroke patients submitted to the CIT protocol for upper extremities present notable changes in the central nervous system (CNS) with improvement in cortical activation and increase of brain areas, using transcranial magnetic stimulation [19–21] or functional magnetic resonance [22–24].

There are still few data about lower extremity constraint-induced movement therapy (LE-CIT). In 2013, a case series was published which had been conducted on multiple sclerosis patients with a 4-year follow-up. At the end of the protocol they observed that these patients showed a notable improvement in *Lower Extremity Motor Activity Log* (LE-MAL) [25].

Although the studies used modified CIT, its methodology was not fully applied. For instance, the intensity applied was lower than that defined by the protocol; the presence of physical constraint on the non-affected side is described (this was discarded as it can create a bigger asymmetry and more abnormal movement); structure of training built without citing shaping (approaching in small steps); adoption of only one exercise, or a simple combination of different therapeutic approaches such as Bobath, muscle strengthening, or climbing stairs [26]; absence of a transference package, or differences in its structure (making only one homework list with exercises instead of a new list every day with different functional tasks); absence of a behavioral contract; and control group not receiving the same intensity of training [27, 28].

Despite not adhering exactly to the recommended model of CIT, these studies observed positive results such as an improvement in motor function, mobility, dynamic balance, discharge weight symmetry, gait ability, gait speed, length and width of step, and force of foot ground contact [26, 28]. However, in view of the above information, the investigation of the effects of the original LE-CIT protocol on gait functionality and balance of chronic hemiparetic patients following a stroke was not completely clarified.

The following research question was established to examine the effects of LE-CIT *vs* intensive conventional therapy on gait functionality and balance, as well as the transference of these gains in therapy to the environment outside the clinical setting in chronic hemiparetic patients following a stroke: is LE-CIT more effective compared with intensive conventional therapy with regard to gait functionality and balance in people suffering from stroke?

## Methods

### Study design

The study adopts a randomized, controlled, single-blinded study design in people suffering from stroke in the chronic stage of recovery. The study has been approved by the local ethics committee at *Associação de Assistência à Criança Deficiente (AACD)* (CAAE: 78269417.9.0000.0085, n° 2.478.704). The protocol will be conducted in the Adults Physiotherapy Department in the Rehabilitation Center of AACD, located at [name]. All participants and their relatives and/or caregivers will provide written informed consent if they are accepted into the study. The study was registered with www.ensaiosclinicos.gov.br (Register Number: RBR-467cv6).

A Consolidated Standards of Reporting Trials (CONSORT) flow diagram of the trial is shown in Fig. 1. and a Checklist of Recommended items to address in a clinical trial protocol and related documents (SPIRIT) is provided in a file.

**Fig. 1 Fig1:**
[figure not shown]
Consolidated Standards of Reporting Trials (CONSORT) flow diagram

### Population

The study population consists of people who had a stroke and want to improve their gait and balance ability. To minimize the chance that improvements occur as a result of spontaneous recovery, only participants who are in the chronic stage of recovery (>6 months after stroke) will be included in the study. The patients will be selected from initial multiprofessional evaluations at AACD. The physicians and physiotherapists will receive a checklist containing the inclusion criteria for this research. The patients who fulfill the criteria will be evaluated by an independent evaluator who is responsible for the screening.

Inclusion criteria for participants: (*i)* Medical diagnoses of stroke (ischemic or hemorrhagic); (*ii*) stroke at least 6 months before study participation; (*iii*) clinically stable; (*iv*) hemiparesis caused by stroke; (*v*) gait deficit caused by stroke (patients perception); (*vi*) able to begin hip and knee flexion on the affected side; (*vii*) able to move from sitting to standing independently even with aid or support of upper limbs; (*viii*) able to transfer while sitting independently; (*ix*) able to sustain body weight on the affected side even with the support of another person and/or aid; (*x*) able to walk at least 10 m with or without aid, with or without support of another person, barefoot; (*xi)* have only one or two main caregivers or relatives who live with the patient or spend substantial parts of the day with them; (*xii*) available to go to the rehabilitation center for 17 consecutive days and stay there for 3 h per day (15 days of treatment and the first day for initial tests and the last day for the final tests); (*xiii*) has not been subjected to orthopedic surgery for at least 6 months at the beginning of the protocol; (*xiv*) has not been subjected to chemical block for at least 3 months at the beginning of the protocol; and (*xv*) does not present an independent community gait (ability of walking alone in the community with or without gait advice at speed of ≤0.8m/s while walking).

Patients will be excluded who (*i*) do not accept the protocol for which they were randomly allocated; (*ii*) have speech deficits that render them unable to understand and/or answer properly to evaluation scales and exercises selected for the protocol; and (*iii*) have suffered any clinical event between the screening and the beginning of the protocol.

Patients will be removed from this trial who (*i*) have two consecutive absences without medical justification and (*ii*) have any clinical intercurrence that makes continuing with the exercises impossible.

Both patient and caregiver will be informed that their participation in this study protocol is totally voluntary and that they are free to discontinue participation at any time. They will also be informed that their treatment and care at AACD will not be affected, regardless of their decision regarding participation in the protocol, but during the 17 days of CIT they cannot enter into another concomitant therapy. The patient will be informed that the recorded data for the final analysis refer to evaluations and treatment applied to this study and that their identity will be always kept confidential. All volunteers will be informed about the potential types of discomfort, the risks, and the procedures employed in the investigation.

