### Randomization, blinding, and treatment allocation

#### Randomization procedure

Randomization will be realized through the allocation of vacancies (21 for each group) by a researcher who has no contact with the evaluation or intervention process. We created a spreadsheet with this sequence of allocation (intervention or control) and the distribution of the participants into the groups was made by sorting the order according to inclusion criteria and recruitment.

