#### Blinding

To minimize evaluation bias, the evaluators responsible for screening and outcome evaluations will be blinded for the group that the patient belongs to. Moreover, the physiotherapist responsible for applying the protocols will not have contact with the test outcomes, but she will be aware of which group the patients belong to. Patients will not be informed to which group they will be allocated. They will probably be able to identify the treatment received, once it is written on the informed consent, but during the protocol they will be asked not to tell the evaluator which kind of treatment they have been submitted to.

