### Measurements

Patient from both groups will be evaluated at 3 time points: T0 - 1° pre-treatment (1–3 days before the beginning of the protocol), T1 - 2° immediately after the end of the protocol (1–3 days after the last day), and T2 - 3° 6 months after the end of the protocol. All the evaluations will be conducted by an independent, blinded, experienced and trained evaluator (Table 1).

**Table 1 Tab1:** Overview of measurements used in this study

Data	Time

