**Self-reported measure**	
LE-MAL	T0, T1, T2

As primary outcomes we have chosen Mini-BESTest and 6min WT, one test for gait performance and one test for balance evaluation.

For the follow-up evaluations, patients will receive, at the end of the protocol, a date to return. Between 30 and 15 days before the date scheduled, we will call them to remember about that. In case of giving up from the protocol we will use all the data collected until the moment of renunciation (it has been predicted at the consent form).

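### Patients who refuse their allocated arm, or who are removed during treatment, leave the trial after randomisation, so the arms compared may not be the arms randomised

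*Protocol article*

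**What the plan says.** Four statements in the protocol article bear on this.

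- **Methods, Population, exclusion (i):** patients are excluded who "do not accept the protocol for which they were randomly allocated".
- **Methods, Population, removal rules:** patients are taken out of the trial if they "have two consecutive absences without medical justification" or "have any clinical intercurrence that makes continuing with the exercises impossible". The text speaks of removal from the trial, not of stopping the sessions.
- **Methods, Measurements (text after Table 1):** "In case of giving up from the protocol we will use all the data collected until the moment of renunciation".
- **Methods, Measurements:** the first outcome visit after baseline, T1, is "immediately after the end of the protocol (1–3 days after the last day" of treatment.

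The Population section also excludes, as criterion (iii), patients who "have suffered any clinical event between the screening and the beginning of the protocol". The article does not say where allocation falls within that interval.

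**The concern.** Randomisation makes the arms comparable only if everyone allocated stays in the comparison. Exclusion (i) selects on the patient's reaction to the arm drawn. The two removal rules select on attendance and health during treatment, both of which the arm can affect.

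The arms differ in burden. According to the Intervention group section, LE-CIT patients attend 3 h/day, sign a behavioural contract, keep a diary and schedule, and carry out daily homework. The Control group section describes 2.5 h/day and none of these additions. If less motivated or less able patients leave mainly from one arm, the remaining patients in that arm look better than those randomised to it, and both primary outcomes (Mini-BESTest and 6minWT) are affected.

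These are rules that the protocol states, not details left to an analysis plan. An analysis plan could not recover T1 and T2 measurements that were never taken.

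**Working it through.** **1. The plan's own figure.** The Sample size section gives an effect size of 0.65 for the 6minWT, a matched-pair t-test, α 0.05 and 0.80 (labelled β, read here as power). For a two-sided paired t-test, power = P(|T| > t(0.975, n−1)), where T is noncentral t with n−1 degrees of freedom and noncentrality 0.65·√n.

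- n = 20: power 0.787. n = 21: power 0.809. The stated 21 reproduces.
- For Mini-BESTest (0.93), n = 12 gives 0.834, so the stated 12 also reproduces.

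The total of 42 is 2 × 21, so nothing is added for loss. On this same calculation, 19, 18 or 17 retained gives power 0.764, 0.739 or 0.711.

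**2. What a lost patient contributes.** Following the rules through:

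| Moment of loss | Data held | Contribution to the between-group change |
|---|---|---|
| Refusal of the allocated arm | T0 at most | none |
| Removal during the 15 treatment days | T0 only | none |
| Giving up between T1 and T2 | T0 and T1 | T0–T1 change only |

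No statement invites refusers or removed patients to T1 or T2.

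**3. Size of a possible bias.** The protocol gives no loss rates, so the inputs here are assumptions: 21 per arm, standard normal outcomes, no true effect, k patients dropped from one arm and none from the other. The k dropped are the lowest on a latent score with correlation c to the outcome. The remaining 21 − k are compared with 21 by a two-sided independent t-test at 5%. The expected shift is c × (mean of the upper 21 − k of 21 ordered normal values). It was simulated with 60,000 trials per scenario.

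| k dropped | Shift, c = 0.5 | Type I error, c = 0.5 | Shift, c = 1 | Type I error, c = 1 |
|---|---|---|---|---|
| 1 | 0.05 SD | 5.5% | 0.09 SD | 7% |
| 2 | 0.09 SD | 6% | 0.17 SD | 10% |
| 3 | 0.12 SD | 7% | 0.25 SD | 14% |
| 4 | 0.16 SD | 8% | 0.32 SD | 19% |

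Check of the formula at k = 3: 0.5 × 0.25 ≈ 0.12. The c = 1 columns are an upper bound, because loss then follows outcome perfectly. Equal losses of the same kind in both arms would largely cancel.

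The shift should not be read as a percentage of 0.65. That figure comes from a matched-pair calculation, whereas the shift is a difference between independent groups.

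**The case against.** The strongest reply is that the protocol does not discard data. It commits to using what was collected before a patient gives up, and a patient who refuses or stops attending can fairly be read as giving up. Inclusion criterion (xii) requires every patient, whichever arm is drawn, to be available 3 h/day for 17 days, which weakens an argument from longer days; the difference in therapy time is only 30 min. The absence rule is also narrow: the absences must be consecutive and without medical justification. All of this stands. None of it supplies T1 or T2 for a patient lost before T1, and the contract, diary and homework still fall on one arm only.

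A reader might infer more than the documents support:

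- **That the planned analysis is per-protocol.** Data analyses names no analysis set, and the commitment to use data up to renunciation points away from strict deletion.
- **That the bias must favour LE-CIT.** No loss rates or reasons are given, so the direction is an inference.
- **That exclusion (iii) is a post-randomisation exclusion driven by the arm.** Its window closes before treatment begins, so treatment cannot cause the event, and allocation is not placed within the window.
- **That exclusion (i) flatly contradicts the Blinding section.** That section says "Patients will not be informed to which group they will be allocated", but adds that patients will probably recognise their treatment from the consent form. There is tension, not outright contradiction.
- **That the sequence was not random.** The phrase "sorting the order according to inclusion criteria and recruitment" is ambiguous, but it stands under a randomisation heading with an independent researcher, and it is a separate matter from losses after allocation.

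**Conclusion.** The point holds for exclusion (i) and the two removal rules. By their wording these take patients out of the trial after randomisation, and the data rule leaves those lost before T1 with baseline data only. The between-group comparison can therefore be biased, plausibly but not certainly towards LE-CIT.

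The size depends on assumptions that the protocol cannot settle. With three patients lost from one arm of 21, a moderate link between loss and outcome (0.5) gives about 0.12 SD and a type I error of about 7%, with about 0.25 SD and 14% as the ceiling. A single loss matters little. The existence of the rules is certain; the magnitude is illustrative. It should be corrected because the trial is small, has no allowance for loss, and depends on both primary outcomes being compared as randomised.

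**What to change.** 1. Delete exclusion (i) as a reason to leave the trial. Obtain willingness to accept either arm at consent, before allocation.
2. In the removal rules, separate stopping the sessions from leaving the trial. The clinical criteria for stopping exercise need no change.
3. Invite every allocated patient to T1 and T2, whatever treatment was received. The article reports data collection as ongoing, so for those already allocated this applies where it is still possible and consent allows.
4. State that the primary analysis includes all randomised patients in their allocated arm, using a method that keeps patients with incomplete follow-up, such as a mixed model for repeated measures. Such a model cannot replace step 3: a patient with T0 alone still carries no information on change. Keep per-protocol as a sensitivity analysis only.
5. Report by arm the number of refusals and removals with reasons. If any patient was excluded under (iii) after allocation, report this by arm and keep the patient in the as-allocated analysis.
6. Reconcile the exclusion and removal rules in Population with the data rule in Measurements, so that one statement governs who is followed and analysed.

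The cost is an amendment, a few extra follow-up visits, and possibly a smaller observed effect because patients who did not complete treatment are counted. Rewording eligibility cannot undo exclusions already made, so steps 3 to 5 carry most of the benefit.

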### Sample size and justification

After a sample size calculation, realized through a pilot study with 10 randomized patients in each group, using G*Power3.1.9.2 Software, we employed a matched-pair t-test *a priori*, using mean and standard deviation of Mini-BESTest (with an effect size of 0.93—sample size of 12 for each group) and 6minWT (with an effect size of 0.65—sample size of 21 for each group) as the primary outcome. Considering for analysis an α 0.05 and β 0.80, 21 patients were estimated for each group, totalizing 42 patients for this study.

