#### Walking performance measures

To evaluate gait performance, we have chosen:

*6-min walk test (6min WT)* [30, 31]: This is used to characterize and monitor the gait changes in patients post stroke. It is commonly used to measure gait endurance and is a significant predictor for gait [32]. A systematic review published in 2017 showed that the clinically important difference (CID) for chronic hemiparesis patients varies from 28 to 42 meters [33].

*Timed up and go (TUG):* This is a simple test for functional mobility that requires the patient to move from sitting to standing, walking 3 m (as fast as possible), turning around (180°), walking back, and sitting again. The latency between letting go of backrest of the chair and then touching the backrest of the chair again after completing the walking is recorded. The best time of three attempts is to be used for the analysis. This is a common test used to evaluate the risk of falling and to monitor changes in patients’ mobility [34]. There is no defined value of CID for stroke patients; however, Hiengkaew et al. [35] shows that a change of ≥28% can indicate a relevant difference.

*10-m walk test (10mWT)*: This is a simple tool to quantify average speed during self-selected gait speed. The patient needs to walk in a hall with a 10-m demarcation, starting 1.5 m before the first mark and stopping 1.5 m after the last mark to exclude acceleration and slowdown. The stopwatch is started when the patient touches or crosses the first line and stopped when they touch or cross the last line. The CID for self-selected speed for stroke patients varies between 0.18 and 0.36 m/s (CI 95%) [35, 36].

*3-D gait analysis (3-DGA)*: This is performed at the Gait Laboratory. Subjects are equipped with skin-mounted reflective markers, placed on specific anatomical landmarks, as described by Kabada et al. [37]. Marker trajectories will be captured by an opto-electronic system consisting of eight infrared cameras (Qualisys OQUS300 system) operating at 100 Hz. Patients are instructed to walk barefoot at a self-selected speed along an 8-m walkway (26 feet). A minimum of six gait cycles for both lower limbs are collected, and a mean of these trials is obtained for the analysis and for consistency evaluation.

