#### Balance measure

*Mini-Balance Evaluation Systems Test (Mini-BESTest)*: This is a tool used to evaluate balance control. It comprises 14 items divided into 4 subscales (anticipatory postural control, reactive postural control, sensory orientation, and gait stability). Each item is classified in an ordinal scale of 3 points (0 = severe and 2 = normal) and the maximum score is 28 points [43–45]. Tsang et al. [46] concluded that the MDC for this tool for post stroke patients is 3 points.

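### The 80% power for the 6-minute walk test holds only for a matched-pair test with a true effect equal to the pilot's 0.65, and is neither a between-arm figure nor tied to the protocol's 28–42 m benchmark

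*Protocol article*

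**What the plan says.** Under Sample size and justification, the protocol article says that the calculation was "realized through a pilot study with 10 randomized patients in each group" and that "we employed a matched-pair t-test". Two inputs are given: the Mini-BESTest "with an effect size of 0.93—sample size of 12 for each group", and the 6-minute walk test "with an effect size of 0.65—sample size of 21 for each group". The error rates appear as "Considering for analysis an α 0.05 and β 0.80", where 0.80 must be read as power. The larger requirement, from the walk test, sets the trial at 21 per group and 42 in total. The section gives no pilot means or SDs, no interval for either effect size, and no target in metres or points.

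Benchmarks appear elsewhere in the article. Under Walking performance measures it reports that "the clinically important difference (CID) for chronic hemiparesis patients varies from 28 to 42 meters". For the Mini-BESTest, under Balance measure, the cited study "concluded that the MDC for this tool for post stroke patients is 3 points". The sample size section refers to neither. The research question at the end of the Background is comparative: LE-CIT against intensive conventional therapy.

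**The concern.** There are three gaps between the stated 80% and the power that a reader will take it to mean.

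- **Test.** A matched-pair t-test describes paired observations. The trial compares two independently randomised arms, and the Randomization procedure describes no matching of patients across arms.
- **Input.** An effect size from 10 patients per group is imprecise, yet it enters as a fixed value with no allowance for that imprecision.
- **Target.** The protocol has its own yardstick for a worthwhile walking gain, but the trial is sized on a standardised number that nobody can convert to metres.

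At stake is whether the power statement describes the trial's main comparison on the outcome that sets its size. As written, it is likely to be read as an 80% chance of detecting a relevant difference between therapies.

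**Working it through.** **Inputs from the protocol article:** effect sizes 0.65 and 0.93; alpha 0.05 (two-sided reproduces the plan, one-sided does not); power 0.80; 21 per group; pilot of 10 per group; 28–42 m. **Assumed:** any SD in metres.

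**1. The plan's own figures.** For a matched-pair t-test with n pairs, the noncentrality is d√n with n−1 degrees of freedom.
- d = 0.65, n = 21: 0.65 × √21 = 2.98, df 20, power 80.9%. The required n is 21.
- d = 0.93, n = 12: 0.93 × √12 = 3.22, df 11, power 83.4%. The required n is 12.

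Both reproduce. The other versions do not: one-sided paired gives 17 and 9, and two-sided independent groups gives 39 and 20.

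**2. The between-arm question.** For two independent groups of n each, the noncentrality is d√(n/2) with 2n−2 degrees of freedom.
- 6-minute walk test, d = 0.65, n = 21: 0.65 × √10.5 = 2.11, df 40, power 54%. For 80%, 39 per arm would be needed.
- Mini-BESTest, d = 0.93, n = 21: 0.93 × √10.5 = 3.01, df 40, power 84%.
- Smallest d detectable at 80% with 21 per arm: 0.89.

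These figures apply if 0.65 and 0.93 are between-arm standardised differences. If they are within-patient changes, step 1 gives the power to detect change over time, and between-arm power cannot be derived from the text.

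**3. Precision of 0.65.** The text does not say how it was computed, so three readings are shown, with noncentral-t 95% limits.

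| Reading | t | df | p | 95% CI for d |
|---|---|---|---|---|
| 10 pairs | 0.65√10 = 2.06 | 9 | 0.07 | −0.05 to 1.32 |
| 10 versus 10 | 0.65√5 = 1.45 | 18 | 0.16 | −0.26 to 1.54 |
| 20 pairs (pre/post, both arms pooled) | 0.65√20 = 2.91 | 19 | 0.009 | 0.16 to 1.13 |

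The paired power at n = 21 can be averaged over this uncertainty. Ten pairs give 67% (flat prior on the effect) or 69% (normal approximation, SE 0.348), and 20 pairs give about 72%. The stated value is 81%. For the Mini-BESTest at n = 21, the paired average over a 10-per-group pilot stays at about 82–85%.

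**4. Link to metres.** 28 / 0.65 = 43 m and 42 / 0.65 = 65 m. So 0.65 SD lies inside the quoted range only if the SD is about 43–65 m, below it for smaller SDs and above it for larger ones.

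Between-arm power with 21 per arm, independent t-test:

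| Assumed SD | Power at 28 m | Power at 42 m | Smallest difference at 80% (0.886 × SD) |
|---|---|---|---|
| 40 m | 60% | 91% | 35 m |
| 60 m | 31% | 60% | 53 m |
| 80 m | 20% | 38% | 71 m |

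For 80% between-arm power, the SD would have to be at most 28 / 0.886 = 32 m for a 28 m difference, or 42 / 0.886 = 47 m for 42 m.

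**The case against.** The strongest reply is that the stated figure is correct on its own terms: given a matched-pair test and d = 0.65, 21 does give 80%. Sizing from a pilot is common practice, the true effect may exceed 0.65, and the second primary outcome holds up (about 84% between arms at 0.93). All of this stands. It limits the point to the walk test and to what the 80% refers to. It does not turn a paired calculation into a between-arm one.

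Three stronger readings are tempting, and the documents do not support them.

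- *The targeted effect is not clinically relevant.* This cannot be shown without an SD. For an SD of 43–65 m, 0.65 lies within the protocol's own range.
- *A null walking result could not be interpreted.* Under Data analyses, the article commits to reporting between-group differences with a confidence interval. That interval can be read against 28–42 m whatever the planned power was.
- *Pilot patients count towards the 42, so the false-positive rate is inflated.* The article does not say that they do, and silence in a condensed article is not evidence. Nor does it say that 0.65 was a comparison by arm. A paired test fits a pre/post change at least as well.

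It would also be wrong to say flatly that the pilot effect is indistinguishable from zero. That is true for 10 pairs or 10 versus 10, but not if 0.65 is a pre/post effect over all 20 patients (p = 0.009).

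**Conclusion.** The point holds in a limited form. The 80% for the 6-minute walk test is conditional on a matched-pair test and on a true effect of exactly 0.65. Neither condition describes the between-arm comparison in the research question. If 0.65 is a between-arm standardised difference, power is 54%. If it is a within-patient change, the text gives no between-arm power at all. The averages of 67–72% depend on how the pilot effect was computed and on the prior used, so they indicate a shortfall rather than measure it.

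Whether 0.65 represents a worthwhile gain is undetermined from the document. The between-arm figures assume a simple two-sample t-test. The planned two-way ANOVA over three time points could be more precise, depending on correlations that are not given. The SDs of 40, 60 and 80 m are illustrative.

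**What to change.** Keep 42 patients and replace the power sentence. The new text should:

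- give between-arm power for the 6-minute walk test at 28 m and at 42 m with 21 per arm;
- give the smallest between-arm difference detectable at 80% for both primary outcomes, in metres and in points;
- state the pilot between-patient SD on which these rest, say what it is the SD of (score or change), and show results over a range around it;
- label 0.65 and 0.93 as pilot estimates, say whether each is a between-arm difference or a within-patient change, and give their confidence intervals.

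The 3-point Mini-BESTest value can be shown for comparison, but the article presents it as a minimal detectable change, so it should not be relabelled as a clinically important difference.

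The cost is one rewritten paragraph and a less favourable stated power for the walk test. No patients are added, and the sponsor should already hold the pilot means and SDs, since the calculation used them.
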